## Statistical analysis

### Sample size justification

The study is powered on between-arm differences in the proportion achieving the primary outcome, minutes per week of moderate-level PA. Our sample size estimation is guided by PA counseling and referral review studies report an effect size between 0.09 and 0.71 for achieving PA guidelines [54–58]. We used the formula given in Vierron and Giraudeau [59] and Vittinghoff and Fitzmaurice [60] with an adjustment for the intraclass correlation coefficient (ICC), where N is the total sample size, the Z’s are the critical value for type I (α = .05) and type II (β = .2) error, σ^2 is the variance in outcome, ρ is the ICC, and π is the proportion (50%) of the N persons assigned to the treatment group. Based on the above formula, assuming an ICC of 0.5 [61], our total sample size of 98 will provide 89% power to detect a 100 min/week of moderate PA difference between groups, corresponding to an effect size of 0.46. Considering an estimated 30% loss to long-term follow-up as reported in similar exercise intervention trials [62], our plan to enroll 98 participants should provide adequate power (80%) to detect differences across intervention arms. Data gathered from those who withdraw from the study will not be used for statistical analyses. This has been accounted for when completing the power analysis, with an additional 20% added to the target sample size. Attrition may be for a number of reasons, which will be ascertained upon withdrawal where possible.

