### Quality assurance and trial coordination

We will implement a clear set of quality assurance steps for trial coordination and delivery of the intervention. Pre-specified recruitment criteria and protocols, rigorous training of personnel at both sites, and monitoring of sites with feedback will help assure high-quality study findings. In order to deliver the multi-level PA intervention strategy uniformly across sites, we will conduct training and certification, provide standardized tools, conduct site-initiation visits, team meetings, and study staff role into each existing patient flow. Data will be collected using standardized tools and instruments. All safety concerns, acute events [e.g., myocardial infarction injuries], or mortality noted during 16-weeks of trial follow-up will be compared between study arms and reported to oversight committees.

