#### Data analysis

Principal Investigators (Stanford University and Emory University) will be given access to the cleaned data sets. Project data sets will be housed on the REDCap hosted by the respective universities and all data sets will be password protected. To ensure confidentiality, data dispersed to project team members will be blinded of any identifying participant information.

Between-group differences in primary and secondary outcomes will be assessed at 8 and 16 weeks. We will test for differences in primary and secondary outcomes to assess treatment effects using multivariate regression models adjusting for baseline characteristics. We will use mixed-effects linear and logistic regression models to predict changes in continuous PA levels and probability of achieving PA recommendations by regressing study arm, study centers, and an interaction between study arm*centers. The mixed model will include one random effect term accounting for the correlation within study center. Analysis of effectiveness will be according to an intention-to-treat analysis including all enrolled and randomized persons into our analysis. Irrespective of compliance with treatment, all participants will be encouraged to continue with the scheduled outcome evaluation until the end of the study. However, as high as up to 30% loss to long-term follow-up would be expected. The characteristics for those participants without complete follow-up will be examined. If missing data is determined to be random, we will perform a sensitivity analysis using multiple imputation-based methods. If missing observations cannot be assumed to be random, pattern mixture models will be considered [64].

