## Discussion

Physical inactivity is a major problem in persons with advanced CKD and transitioning to dialysis and a modifiable risk factor for many important outcomes including function, quality of life, and mortality. Several attempts have been made to make exercise more convenient for CKD patients by different intervention modalities such as intradialytic exercise programs using cycle ergometers [21] and various resistance exercise programs [65]. Despite these attempts at tailored interventions, patients are not adhering to exercise regimens. When Konstantinidou et al. [66] compared intradialytic exercise, home based exercise, and rehabilitation center-based exercise, the group that participated in the intradialytic exercise program had a dropout rate of 16.7%, as compared to 23.8% dropout rate for patients in the rehabilitation center-based group and 16.7% in the home-based exercise group.

In order for clinicians and health care systems to create tailored exercise interventions that promote exercise adherence, further examination of barriers to and motivators for exercise in CKD patients is needed. Our interdisciplinary approach includes vital input from the target populations, fosters physician-patient interactions around this topic, and is based on use of existing clinical and community resources, supplemented with trained EIM fitness professionals for whom we will develop a curriculum specific to persons with advanced kidney disease. If shown to be efficacious and effectively implemented, our research will be translatable immediately within the two major practices involved in the study and with modest effort, to other practices within the region.

Our previous “proof of principle” feasibility study which compared the effectiveness of the supplemented EIM protocol (PA vital sign + exercise referral arm) compared to the EIM protocol alone (PA vital sign) in the general population demonstrated a greater improvement in PA among individuals in the referal group (changes in self-reported PA: rerefal group: + 250 min/week vs.

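### The protocol excludes all data from participants who withdraw, yet promises an intention-to-treat analysis of everyone randomised; extra enrolment does not make up for the exclusion

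*Protocol article*

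**What the plan says.** Two sections of the protocol article give a rule for people who leave the trial.

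- **Sample size justification:** "Data gathered from those who withdraw from the study will not be used for statistical analyses". The next sentence offers the remedy: "This has been accounted for when completing the power analysis, with an additional 20% added to the target sample size". The same paragraph expects 30% loss to long-term follow-up.
- **Data analysis:** "Analysis of effectiveness will be according to an intention-to-treat analysis including all enrolled and randomized persons into our analysis". It adds: "Irrespective of compliance with treatment, all participants will be encouraged to continue with the scheduled outcome evaluation until the end of the study". For missing data it says: "If missing data is determined to be random, we will perform a sensitivity analysis using multiple imputation-based methods". Otherwise, "If missing observations cannot be assumed to be random, pattern mixture models will be considered".

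The primary outcome (Expected outcome section) is the between-group difference in change in weekly minutes of moderate-to-vigorous activity at 16 weeks. The minutes come from a wearable synchronised every week (Primary outcome section), and visits are planned at 8 and 16 weeks. Someone who withdraws before week 16 will therefore usually leave usable earlier data.

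**The concern.** A randomised participant who withdraws is out under the first rule and in under the second. Nothing confines the exclusion to a per-protocol or secondary analysis, and nothing ranks the two rules. An analyst could defend either one after seeing the data.

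The exclusion is also the wrong rule for this trial. Dropping people according to something that happens after randomisation means the groups compared are no longer those that randomisation formed. According to the Randomization section, participants and clinical staff know the assignment once the intervention starts, and only group 2 is asked to attend twice-weekly classes. Withdrawal that depends on arm or on response is therefore plausible.

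The justification offered does not answer this. Enlarging the sample compensates for lost precision and does nothing about who was lost.

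**Working it through.** **1. The two rules side by side**

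| Question | Sample size justification | Data analysis |
|---|---|---|
| Is a randomised person who withdraws analysed? | No | Yes |
| Are that person's baseline, week-8 and weekly wearable data used? | No | Yes; imputation and pattern-mixture models draw on them |
| How is the loss handled? | 20% more participants | Missing-data models |

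The Data analysis section does not rescue the exclusion. Multiple imputation is only a sensitivity analysis there, pattern-mixture models are only to be considered, and neither can use data already set aside. This contradiction needs no arithmetic.

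**2. The plan's own power figure**

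Inputs from Sample size justification: N = 98 (49 per arm), effect size 0.46, ICC 0.5, α = 0.05. A two-sided test and a variance multiplied by (1 − ICC) are my assumptions; they reproduce the stated 89%.

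- Power = Φ(0.46 / (√0.5 × √(2/49)) − 1.96) = Φ(3.22 − 1.96) = 89.6%.
- Implied SD = 100 / 0.46 = 217 min/week.
- Same formula with 20% lost (39.2 per arm): 82.1%. With 30% lost (34.3 per arm): 76.9%.

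Power is the only thing that the allowance affects.

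**3. Why a larger sample does not help**

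Excluding withdrawers shifts the estimated difference by

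bias = d₂ × gap₂ − d₁ × gap₁,

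where d is the share withdrawing in an arm and gap is the completer mean minus the withdrawer mean. Sample size does not appear. Suppose there is no true effect and the bias is 30 min/week (an assumed value, chosen only to show the pattern). With SE = 217 × √0.5 × √(4/N), the two-sided false-positive rate is:

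| Number analysed | False-positive rate |
|---|---|
| 69 | 12.8% |
| 98 | 16.2% |
| 200 | 28.1% |
| 400 | 49.7% |

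With zero bias it is 5% throughout. If there is bias, more participants make a false positive more likely.

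**4. Illustration with the cited dropout rates**

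The Discussion cites a "23.8% dropout rate for patients in the rehabilitation center-based group and 16.7% in the home-based exercise group". Apply 23.8% to group 2 and 16.7% to group 1, and assume the same latent correlation r between staying and outcome in both arms. The completer mean in an arm then shifts by r × φ(z_p)/(1 − p) × SD.

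- p = 0.238: 0.3095/0.762 = 0.406; × 217.4 = 88.3.
- p = 0.167: 0.2502/0.833 = 0.300; × 217.4 = 65.3.
- Difference: 23.0 × r, which is 4.6, 6.9 and 11.5 min/week for r = 0.2, 0.3 and 0.5.

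That is 0.02 to 0.05 SD. With about 34 analysed per arm and the full SD (SE = 217.4 × √(2/34.3) = 52.5), the false-positive rate is 5.1% to 5.6%, close to nominal. The values of r are assumptions, and the cited programmes only loosely resemble groups 1 and 2.

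**The case against.** The strongest reply is that one sentence in a sample-size paragraph should not be read against a dedicated analysis section that names intention to treat, encourages follow-up regardless of compliance and plans missing-data methods. Withdrawing from the study may also be narrower than loss to follow-up: the paragraph attaches the exclusion to a 20% allowance but expects 30% loss. People lost without formally withdrawing would then stay in the analysis. This limits how many people the exclusion touches. It does not remove the conflict, because the exclusion is unqualified.

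Three stronger readings are tempting, and the document does not support them.

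- **The exclusion inflates the effect, by a large amount.** A reader might reason that if completers differ by 100 min/week and the 30% who withdraw gain nothing, the effect in all randomised is 0.7 × 100 = 70, an overstatement of 43%. Or, with poor responders leaving group 2 and purely random loss in group 1, that false-positive rates reach 7% to 18%. Both scenarios apply the exclusion to the full 30% loss and assume the pattern of withdrawal that produces inflation. Outcome-related loss in group 1 could offset or reverse the bias. These figures also reflect week-16 outcomes that were never observed. Deleting the sentence recovers earlier data, so it repairs the bias only as far as those data predict the missing minutes.
- **Adverse events of withdrawn participants would be lost.** The Quality assurance and trial coordination section has a specific rule: "All safety concerns, acute events [e.g., myocardial infarction injuries], or mortality noted during 16-weeks of trial follow-up will be compared between study arms". A general sentence about sample size is weak ground for overriding it.
- **Information on barriers to retention would be lost.** The same sample-size paragraph plans to record reasons for attrition where possible, and the Data analysis section plans to examine the characteristics of those without complete follow-up.

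**Conclusion.** The plan is wrong as written. It gives two incompatible rules for the primary analysis set, and it presents a sample-size allowance as the answer to an exclusion that can cause bias. Confidence in the contradiction is high, and it rests on the text alone.

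The consequence is conditional. Following the exclusion biases the 16-week comparison if withdrawal is related to outcome or differs by arm. That is plausible here, but neither its size nor its direction can be derived from the document. The 5 to 11 min/week obtained with the cited dropout rates is an illustration that depends on the assumed correlations and on equal selection in both arms. It is neither an estimate nor a bound.

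**What to change.** - Delete the exclusion sentence and the statement that the added 20% accounts for it.
- State one rule: every randomised participant is analysed in the assigned arm, using all data collected up to withdrawal (baseline, week 8 and weekly synchronised minutes) in the mixed or imputation model.
- Label any completers-only analysis as supportive.
- State that the attrition allowance covers precision only.

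The cost is protocol wording and a little more analysis work, with no extra participants or visits. The headline estimate may be less favourable than a completers-only one.

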## Expected outcome

Our primary outcomes is between-group difference in change in minutes/week of moderate-tovigorous PA between group 1 and 2 at 16 weeks. Based on our previous work, we expect greater improvement in grip strength, 6- min walk test, and PA among group 2 compared to group 1 participants. [54, 63]

### Quality assurance and trial coordination

We will implement a clear set of quality assurance steps for trial coordination and delivery of the intervention. Pre-specified recruitment criteria and protocols, rigorous training of personnel at both sites, and monitoring of sites with feedback will help assure high-quality study findings. In order to deliver the multi-level PA intervention strategy uniformly across sites, we will conduct training and certification, provide standardized tools, conduct site-initiation visits, team meetings, and study staff role into each existing patient flow. Data will be collected using standardized tools and instruments. All safety concerns, acute events [e.g., myocardial infarction injuries], or mortality noted during 16-weeks of trial follow-up will be compared between study arms and reported to oversight committees.

#### Data analysis

Principal Investigators (Stanford University and Emory University) will be given access to the cleaned data sets. Project data sets will be housed on the REDCap hosted by the respective universities and all data sets will be password protected. To ensure confidentiality, data dispersed to project team members will be blinded of any identifying participant information.

Between-group differences in primary and secondary outcomes will be assessed at 8 and 16 weeks. We will test for differences in primary and secondary outcomes to assess treatment effects using multivariate regression models adjusting for baseline characteristics. We will use mixed-effects linear and logistic regression models to predict changes in continuous PA levels and probability of achieving PA recommendations by regressing study arm, study centers, and an interaction between study arm*centers. The mixed model will include one random effect term accounting for the correlation within study center. Analysis of effectiveness will be according to an intention-to-treat analysis including all enrolled and randomized persons into our analysis. Irrespective of compliance with treatment, all participants will be encouraged to continue with the scheduled outcome evaluation until the end of the study. However, as high as up to 30% loss to long-term follow-up would be expected. The characteristics for those participants without complete follow-up will be examined. If missing data is determined to be random, we will perform a sensitivity analysis using multiple imputation-based methods. If missing observations cannot be assumed to be random, pattern mixture models will be considered [64].

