### Baseline data collection

Data collection will occur at baseline and at 8- (V1) and 16 weeks (V2) after the interventions (Table 2). Personal information, including relevant medical history will be collected prior to the initiation of testing or intervention upon receiving participant consent. This will include patient characteristics of age, sex, basic anthropometric measures (height, weight, BMI and waist circumference), relevant comorbidities and medications.

**Table 2 Tab2:** Interventions examples

Class format	Minutes	Teachable moments
a. Strong bones and healthy hearts		
Warm-up and rhythmic stretch	10–12	• Pre-Warm-Up: Perceived exertion, breathing and hydration. • Action Planning: ROM safety through major/minor joints. • Warm-up: Large to small muscles.
Circuit Choreography	15	• Selecting the right tubing resistance, benefits of strength work, benefits of cardio work & the plus for both in a circuit format. • Resistance tubing safety. • Breathing techniques for strength work. • Cardio-cognitive benefits • Benefits of tempo changes through half-time, at music tempo and double- time tempos. • Benefits of non-dominant side movements.
Cool-Down	5	• Benefits of lowering the heart rate progressively.
Core Strengthening	5	• Benefits of concentric, eccentric strength training.
Flexibility Training	5–8	• Option - Chair transfer technique from chair to floor and from floor to chair. • Range of Motion versus Range of Movement.
Relaxation & Future Action Planning	5–10	• Breaking the symptom cycle and self-managing pain, fatigue, frustration, etc.
b. Stability & Balance for Fall Prevention		
Warm-up and rhythmic stretch		• Pre-Warm-Up: Perceived exertion, breathing and hydration. • Action Planning: ROM safety through major/minor joints. • Warm-up: Large to small muscles.
Core stability and strength training	5	• The muscle groups which compose the core. • Benefits of breathing for increasing abdominal chest wall strength and flexibility
Balance training	5–10	• Agility – changing center of gravity • Lower body strength
Stability training	5–10	• Stability in an unstable environment • How to protect the lower back during extensions • PNF stretching principles
Flexibility	10	• Stretch tight muscles for better posture • Use breathing to deepen stretches
Relaxation and Action planning	10	• Breaking the symptom cycle to better self-manage pain, fatigue, fear, anger, frustration and physical instabilities

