Fitness professionals will follow the 2008 PA guidelines safety recommendations for PA programming tailored to persons with CKD and will be trained on communication skills and behavioral techniques (goal-setting, action planning, self-monitoring, provide instruction, feedback on performance, opportunities for social comparison, peer modeling, and social support) [45]. Two sessions/week will be offered, slowly progressing towards 50 min of light-to-moderate PA per session. Persons will also be encouraged to accumulate additional minutes of moderate PA throughout the week, primarily through increased walking for leisure and transportation. Interventions are structured around “*Move and Learn*” formats. They will include health education, led PA and lifestyle behavior change segments modeled after evidence-based sources (interventions examples are shown in Table 3) [46]. The social dynamics of the group will be used to forge strong, sustainable relationships with participants and reach appropriate minutes per week of PA, collect data using Health IT resources and provide guidance at the end of 8-week core intervention for transitioning to maintenance and self-managed PA. We will continue to offer the intervention even if the the participant initiates dialysis. For particiapnts who recently underwent surgery for dialysis access, we will encourage participation but limit arm exercise.

**Table 3 Tab3:** Study Procedures and measurements

	Baseline	Follow-up: 1	Follow-up: 2
		8 weeks	16 weeks
Self-reported			
Physical activity vital sign	√		
Medical history (or any changes thereof)	√	√	√
Quality of life (SF-12)	√	√	√
Qualitative Interview^a^	√		
Adverse events		√^b^	√
MEASUREMENTS			
Grip strength	√	√	√
6-min walk test	√	√	√
Anthropometry (measured BMI, waist circumference)	√	√	√
Blood pressure and blood glucose level	√	√	√
Weekly physical activity as measured by Garmin PA monitor	√	√^b^	√
INTERVENTIONS			
Brief physical activity counseling	√		
Wearable physical activity monitor	√	√	√
Group exercise sessions		√	

^a^in a subset of patients recruited at start of study

^b^assessed continually during the study in G2

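### The analysis section is unclear on whether the activity model is baseline-adjusted; baseline Garmin minutes per week should be named as a covariate

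*Protocol article*

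**What the plan says.** The Expected outcome section of the protocol article defines the primary outcome as the "between-group difference in change in minutes/week of moderate-tovigorous PA between group 1 and 2 at 16 weeks".

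The Data analysis section then makes two statements in succession. Treatment effects on primary and secondary outcomes will be tested with "multivariate regression models adjusting for baseline characteristics"; the characteristics are not listed. Next, mixed-effects linear and logistic models will "predict changes in continuous PA levels and probability of achieving PA recommendations by regressing study arm, study centers, and an interaction between study arm*centers", with one random term for study centre. Neither sentence names baseline activity.

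The only place that itemises patient characteristics at baseline is Baseline data collection: "This will include patient characteristics of age, sex, basic anthropometric measures (height, weight, BMI and waist circumference), relevant comorbidities and medications". Activity is not in that list. Table 3 does schedule it: the row "Weekly physical activity as measured by Garmin PA monitor" is ticked at baseline, 8 weeks and 16 weeks.

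**The concern.** A reader who fits the model from its listed terms will regress change in minutes per week on arm, centre and their interaction, with no baseline value. A reader who relies on the sentence before will adjust for something, but cannot tell whether the baseline value of the outcome is included. These are different analyses of the primary outcome.

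Efficiency is at stake, not bias. In a randomised comparison an unadjusted change score estimates the right quantity, but it can carry baseline noise into the response and it leaves chance baseline imbalance only crudely handled. With 96 participants planned in the Abstract, 98 in the sample size section, and up to 30% loss expected, precision that costs nothing is worth taking.

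**Working it through.** **Inputs from the protocol article.** Sample size justification: N = 98, 1:1 allocation, α = 0.05 (two-sided assumed), difference 100 min/week, effect size 0.46 (so an SD of 100/0.46 ≈ 217 min/week), ICC 0.5, stated power 89%. Table 1: entry requires self-reported moderate activity below 30 min/week. **Not in the document:** the correlation r between baseline and follow-up, and the baseline SD s0. Both are assumed below.

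**The plan's own figure.** Power = Φ(√(N/4 × 0.46²/f) − 1.96), where f is a variance factor. With f = 1 − 0.5 = 0.5 and N = 98: 24.5 × 0.2116 = 5.184; 5.184/0.5 = 10.368; the square root is 3.220; Φ(1.260) = 89.6%. The stated 89% reproduces, and nothing below depends on it.

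**Change score against baseline adjustment (linear model).**

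- Var(change) = s1² + s0² − 2·r·s0·s1
- Var(adjusted) = s1²(1 − r²)
- Difference = s0² − 2·r·s0·s1 + r²·s1² = (s0 − r·s1)²

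The difference is never negative, and it is zero exactly when r = s0/s1. With equal SDs the ratio adjusted/change is (1 − r²)/(2(1 − r)) = (1 + r)/2.

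In units of s1²:

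| s0/s1 | r | Change | Adjusted | Ratio | Saving |
|---|---|---|---|---|---|
| 1 | 0.3 | 1.40 | 0.91 | 0.65 | 35% |
| 1 | 0.5 | 1.00 | 0.75 | 0.75 | 25% |
| 1 | 0.7 | 0.60 | 0.51 | 0.85 | 15% |
| 0.5 | 0.3 | 0.95 | 0.91 | 0.96 | 4% |
| 0.5 | 0.5 | 0.75 | 0.75 | 1.00 | 0% |
| 0.5 | 0.7 | 0.55 | 0.51 | 0.93 | 7% |

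The saving does not simply fade as the baseline SD shrinks. At s0/s1 = 0.25 the ratios are 0.997, 0.923 and 0.716, so savings of about 0%, 8% and 28%.

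**Does adjusting change the primary outcome?** No. If change = a + b·arm + c·baseline, then week-16 minutes = a + b·arm + (c + 1)·baseline. The arm coefficient b is the same, so the outcome can stay defined as change.

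**Is the baseline value usable?** The Randomization section places randomisation before baseline testing. The section on the wearable monitor says the device can be regarded as part of the intervention. Table 3 ticks the Garmin measurement, the wearable and the counselling all in the baseline column. No wear period ahead of counselling is described.

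**The case against.** The strongest reply is that the sentence before the model already promises baseline adjustment for the primary outcome. The mixed-model sentence may only describe the structure of that same adjusted analysis, and an article may leave the covariate list to an analysis plan. Nothing labels the mixed model as the primary one, and no sentence excludes baseline activity. Having change as the response is no evidence of omission either, since it is compatible with a baseline covariate. All of this stands: omission is the plain reading of the listed terms, not a certainty. What remains is that the article does list terms, that the list lacks the baseline value, and that the adjacent sentence points the other way.

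Three stronger readings are tempting and not supported.

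- A reader might infer that the change score loses precision unless baseline and follow-up are almost perfectly correlated. That needs equal SDs. In general the loss vanishes at r = s0/s1, and the entry limit on activity makes a smaller baseline SD possible. The limit is self-reported, however, so it may restrict Garmin minutes only loosely.
- A reader might infer a power gain from 62.4% to 74.8% at N = 98. That needs equal SDs, r = 0.5, no ICC factor and 0.46 read against the follow-up SD. With s0 half of s1 and r = 0.5, both analyses give 74.8%. If 0.46 is instead on the change scale, with equal SDs, the unadjusted figure stays at 62.4% and adjustment gives 80.6%, 74.8% or 69.5% at r of 0.3, 0.5 or 0.7. The document does not say which SD is meant.
- A reader might infer that adjustment would rescue the stated 89%. That figure uses a variance factor of 0.5. At r = 0.5 with equal SDs, neither the change score (1.00) nor the adjusted analysis (0.75) reaches it. This is a separate sample-size question.

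**Conclusion.** The point holds as an inconsistency with a modest, uncertain cost. The two sentences leave it open whether the activity model is baseline-adjusted, and the listed terms describe an unadjusted change score. That analysis would be valid but, in large samples, at best as precise as the adjusted one. The saving in variance, equivalently in participants for the same power, is 15 to 35% for r between 0.7 and 0.3 with equal SDs, and about 0 to 7% at the same r values if the baseline SD is half the follow-up SD. Both r and s0 are assumptions, so no single power loss can be attributed to this trial. The variance argument covers the linear model for minutes, not the logistic model.

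**What to change.** Reconcile the two sentences in Data analysis. State that the 16-week model contains arm, the centre terms and baseline Garmin minutes per week as a covariate, with either change or week-16 minutes as the response. Say likewise that the 6-minute walk, grip strength and questionnaire scores are each adjusted for their own baseline value. These baseline values need only be named in the text, and a line is needed on how a missing baseline covariate is handled, for example by simple imputation.

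State also that the baseline Garmin value must come from wear before counselling and classes, so that the covariate is not itself affected by the intervention. A change score computed from that baseline has the same need. If the schedule already has such a wear period, this is wording only; if not, it is a small procedural change.

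### With two centres, the mixed model enters centre as both fixed and random, and its arm-by-centre term leaves the overall treatment contrast undefined

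*Protocol article*

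**What the plan says.** Under Data analysis, the article describes mixed-effects linear and logistic models for continuous activity and for meeting activity recommendations, fitted "by regressing study arm, study centers, and an interaction between study arm*centers". The random part is then given: "The mixed model will include one random effect term accounting for the correlation within study center". No other random effect, covariance structure, visit term, factor coding or contrast is named. The same section states that "Between-group differences in primary and secondary outcomes will be assessed at 8 and 16 weeks". It also names a baseline-adjusted regression for testing treatment effects, and does not say which of the two models is primary.

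The abstract and Research setting and team give two sites, Atlanta and the Bay Area. Expected outcome sets the primary outcome as the between-group difference in change in weekly moderate-to-vigorous activity at 16 weeks, which is one change per participant. Sample size justification powers a single overall difference: "our total sample size of 98 will provide 89% power to detect a 100 min/week of moderate PA difference between groups". It puts the standardised effect at 0.46 and the ICC at 0.5.

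**The concern.** The model is written out, so this is a matter of what the article fixes rather than of detail left to an analysis plan. Three features need attention.

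- **Centre appears twice.** Two fixed centre parameters already fit the two centre levels exactly, so a random centre intercept has nothing left to estimate.
- **Arm-by-centre sits in the effect model.** The model then has no single arm effect until a coding or contrast is chosen. Two analysts could follow the text faithfully and report different treatment effects, with different standard errors. The two clinics serve different populations, so an effect at one need not equal the overall effect.
- **The only random effect is for centre.** If week-8 and week-16 values entered this model together, the correlation within a person would be ignored.

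At stake is whether the reported arm effect is the overall 16-week difference that the trial was sized to detect, and with what precision.

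**Working it through.** **Inputs (Sample size justification).** N = 98; difference 100 min/week; effect size 0.46; ICC 0.5; equal allocation ("π is the proportion (50%) of the N persons assigned to the treatment group"); α = 0.05, with sidedness not stated and two-sided assumed; 30% loss. I take the ICC as given.

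**Reproducing the plan's power.** The implied SD is 100/0.46 = 217.4 min/week. With individual randomisation within centres, the ICC reduces the variance by the factor 1 − ρ, so the working SD is 217.4 × √0.5 = 153.7.

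- SE of the arm effect = 2 × 153.7/√98 = 31.1 min/week.
- Power = Φ(100/31.1 − 1.96) = 0.896, against 89% stated (0.890 at N = 96).
- After 30% loss (68.6 evaluable), SE = 37.1 and power = 0.769. The plan states 80% here.

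**Centre as fixed and random.** The arm effect is a comparison within centres, and a centre intercept is common to both arms, so it cancels. I confirmed this in 150 simulated data sets of 98 participants in two equal centres. Compared with an ordinary fixed-centre regression, the model with centre in both parts gave the same arm estimate (largest difference below 10⁻¹²) and the same SE (ratio 1.000). Only the SE of the centre term was distorted: 220 against 44.

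**Arm-by-centre.** Write the mean as b0 + b1·A + b2·C + b3·A·C.

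- With C coded 0/1, the arm effect is b1 at the reference centre and b1 + b3 at the other. The overall effect is b1 + w·b3, where w is the weight given to the second centre. The article fixes neither the coding nor w.
- Reading b1 as the result, with equal centres, uses 49 participants: SE = 2 × 153.7/√49 = 43.9, which is √2 times 31.1.

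| Contrast (equal centres) | Power, N = 98 | Power after 30% loss |
|---|---|---|
| Arm effect from main-effects model | 0.896 | 0.769 |
| Arm coefficient, 0/1 coding with interaction | 0.624 | 0.478 |

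If the reference centre holds 30% to 70% of the 98 participants, the second row's power at N = 98 ranges from 0.42 to 0.77. With centred coding, the arm coefficient is the average over centres. Its mean SE in the simulation was 30.9, so nothing is lost.

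**Repeated values, only if pooled.** Suppose both visits enter one model with no participant term. The two-sided type I error of the arm test is 2 × [1 − Φ(1.96/√(1 + r))], where r is the within-person correlation (assumed, since the article gives none).

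| r | Formula | Simulation, 4,000 data sets |
|---|---|---|
| 0.3 | 0.086 | not run |
| 0.5 | 0.110 | 0.107 |
| 0.7 | 0.133 | 0.139 |

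Analysing week 16 alone in the same simulations gave 0.046 to 0.048, which is nominal.

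**The case against.** The strongest reply is that none of this need harm the result. The duplicated centre term leaves the arm comparison untouched. The article never says that a single-centre coefficient will be reported: Expected outcome and Data analysis both speak of the difference between groups, and coding and contrasts are commonly left to an analysis plan. Expected outcome sets one change per participant at 16 weeks, and nothing says that the two visits share a model. Separate models at each visit are the natural reading, and they need no participant term. The article does not call the mixed model primary either.

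Much of this stands. A reader might infer that the treatment effect and its standard error are simply wrong, or that the type I error is inflated. The documents support neither. The first needs a choice of coding and contrast that the article does not make, and the second needs a pooled model that it does not describe. The power loss above is therefore the cost of one permissible reading.

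The reply does not remove the specification problem. The article commits to an interaction and to a random effect for two centres. The first leaves the powered overall difference without a defined estimate, and the second can estimate nothing.

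**Conclusion.** The point holds as a badly fixed specification. The mixed model is over-specified for two centres, which does not affect the arm estimate or its standard error. It also includes arm-by-centre without naming the contrast that represents the overall treatment effect. If the 0/1-coded arm coefficient is read as that effect, power falls by about 27 percentage points at N = 98 (0.90 to 0.62) and by about 29 after 30% loss (0.77 to 0.48). A centre-averaged contrast avoids this.

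The figures rest on a two-sided 5% test, equal centres, and the plan's effect size and ICC with variance reduced by 1 − ρ. The missing participant term is a conditional point: type I error would be about 9% to 13% for assumed correlations of 0.3 to 0.7, but only if the two visits were pooled. This is a clarification to settle before outcome data are analysed. It does not show that the planned inference is invalid.

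**What to change.** State one model for the primary outcome:

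- **Outcome:** 16-week change in weekly moderate-to-vigorous activity.
- **Terms:** arm, centre as a fixed effect only, and baseline activity. Remove the centre random effect.
- **Treatment effect:** the arm contrast at week 16 from this main-effects model.
- **Arm-by-centre:** fitted only in a separate model labelled exploratory.
- **If weeks 8 and 16 are modelled jointly, and only then:** add visit, arm-by-visit, and a participant random intercept or an unstructured within-person covariance. The primary contrast stays at week 16.

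The change is to wording only and needs no extra data or participants. On the plan's inputs, the main-effects contrast keeps power at 0.896 for N = 98. The price is that site-specific effects become exploratory.
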